### Statistical and Qualitative Analyses

Focus group transcripts will be analyzed using inductive thematic analysis. This inductive approach is useful when using direct questions to describe a particular experience and find common themes within data [43]. Two researchers will go through multiple coding iterations, with the first consisting of coding the data without preconceived categories. After the first round of coding, the researchers will decide on what codes to use and apply finalized codes using Atlas.ti (Lumivero) software [44]. Consistency will be achieved through regular team meetings, coding disagreements will be resolved through team deliberation, and code definitions will be enhanced as needed [45,46]. An in-depth review of coded data will lead to the identification of themes related to the safety, acceptability, and potential reach of the MOUD Hub and its hypothesized usefulness in improving access to and retention in MOUD treatment. We will then conduct member checking with selected participants to reduce the risk of data misinterpretation [47,48]. We will keep a log of suggestions and reasons regarding why they were or were not implemented.

Open-ended responses to the pop-up survey in the MOUD Hub will be analyzed on Atlas.ti software by the same 2 researchers using deductive-inductive thematic analysis based on the codebook developed for the analysis of the focus groups’ data but allowing for new codes to emerge [49]. The same process will be followed to reach a consensus on the coding and to identify themes to answer our research questions.

Descriptive statistics will be conducted to assess the population that has accessed the website, their website of origin (Reddit or Google), how long participants were on the website, and how many pages they visited. Descriptive statistics will include the percentages, means, and SDs of age, gender, and geographic location of users. Descriptive statistics on how long participants were on the website and how many pages they visited will be measured by the total number of times the web page was visited, how many pages were visited, and the proportion of returning users. Descriptive statistics on the mean and SD of responses to the Acceptability of Intervention Measure will be assessed, with a mean between 4 and 5, corresponding to the “agree” and “completely agree” options in the scale, interpreted as users finding the website acceptable. We will produce CIs for each outcome.

Bivariate statistics, such as 1-tailed *t* tests, will be used to examine the difference in outcomes between users who come from Reddit and those who come from Google. Similarly, we will investigate differences in sociodemographic characteristics and use patterns of the website by conducting bivariate *t* tests. We will apply statistical tests to identify significant differences in the number of times each stage was accessed (vs all other stages) and in the number of times each specific resource was clicked on (vs other resources within that stage).

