There are no eligibility criteria for the study when assessing the website’s reach due to it being available for public access. We will be openly advertising it to people who make relevant Google searches or who are members of opioid-related subreddits. Similarly, there is no randomization, as all users can access the same website’s content. We will be able to identify whether participants came from Reddit or Google and treat them as 2 different samples. This will enable us to investigate differences in user volume and characteristics when accessing the website through Reddit or Google and to evaluate the most appropriate platform for dissemination for future-related interventions.

There is potential for bias, including misclassification, self-selection, and response bias. It will not be possible to know whether users are experiencing OUD or searching for information for a loved one, limiting our understanding of the representativity of the sample by OUD experience and leading to potential misclassification bias. However, we will be able to know whether users clicked on resources specific to friends or family and whether they responded to the “check-in” questions directed at people living with OUD. In addition, the pop-up survey asks whether users are accessing the website for themselves or a friend or family member. This will provide us with an additional measure for the proportion of users who are seeking help for themselves versus for a friend or family member.

Effectively, all people accessing the website will self-select based on need or curiosity, and we will miss information from people living with OUD who are not seeking help for OUD or are not compelled to access the *MOUD Hub* when exposed to it. The demographics data will allow us to assess to what extent our sample is representative of the general population and the population experiencing OUD and fatal overdoses in the United States in terms of geography, age, and gender. We will also be able to assess whether users are accessing the website from Google, Reddit, or other sources, potentially representing different communities. While response bias is possible in the context of our pop-up survey, participation will be voluntary and anonymous, and therefore, this will be minimized. However, there will undoubtedly be self-selection bias among the group answering the survey, likely representing those most engaged in improving access to reliable MOUD information*.*

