**Figure 4 figure4:**
[figure not shown]
A pop-up survey that will be presented to users before they leave the website to collect demographic information and initial acceptability of the website. MOUD: medications for opioid use disorder.

To further assess acceptability, we will measure the proportion of users who return to the website along with using the Acceptability of Intervention Measure [41]. The pop-up survey will ask closed- and open-ended questions to assess acceptability and identify additional relevant resources. The closed-ended questions will use the 4 questions from the Acceptability of Intervention Measure [41]. The open-ended questions will ask about ways in which they found resources helpful, whether there are other topics or questions that they expected to obtain information on but did not find anything relevant, and whether there are any other resources they would like to share with the broader community. Google Analytics tracks the number (and proportion) of people who are returning users, which will be used as another measurement of acceptability.

Finally, we will compare users who come from Reddit versus those who come from Google by looking at the volume of users from each source and their characteristics. The aforementioned outcomes will be assessed to compare the effectiveness of social media versus search engines in disseminating resources such as the *MOUD Hub.*

For the website’s reach, we hypothesize that (1) users will most frequently click on links related to the precontemplation or contemplation phases of MOUD use, as opposed to links related to the preparation, action, and maintenance phases; (2) a substantial proportion of users (>25%) will be family members or friends of people who use opioids; (3) the volume of users referred through Google searches will be larger than that of users referred through Reddit; and (4) users referred through Reddit will spend more time on the website and click on a higher number of links than users referred through Google searches.

For acceptability, we hypothesize the following: (1) most users will find the resource useful and ratings will be significantly higher among acquaintances of people who use opioids than among people who use opioids themselves; (2) users with OUD will find the resource less useful; and (3) a large proportion of resources shared by users will lead to non–evidence-based information, including rehabilitation centers based on mandatory abstinence.

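### Reddit–Google comparison: the only named test is a t test (1-tailed for outcomes, with no direction assigned), which does not suit outcomes without a predicted direction, nominal variables, or one user total per source

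*Protocol article*

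**What the plan says.** Two sentences in Statistical and Qualitative Analyses of the protocol article govern the comparison by referral source. The first covers outcomes: "Bivariate statistics, such as 1-tailed *t* tests, will be used to examine the difference in outcomes". The second covers user characteristics and use: "we will investigate differences in sociodemographic characteristics and use patterns of the website by conducting bivariate *t* tests". The first offers the 1-tailed t test as an example. The second has no such qualifier, but it does not repeat that the test is 1-tailed. Neither gives a direction for any variable.

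Outcomes and Measures sets out what is compared. The two sources are contrasted "by looking at the volume of users from each source and their characteristics", and the comparison is then widened to all outcomes described earlier in that section. Table 2 lists these: volume, time on site, resources clicked, demographics (age, gender, location, language, and whether the visit is for oneself or for someone else), the proportion returning, and the Acceptability of Intervention Measure.

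Two of the reach hypotheses concern source. Hypothesis 3 is that "the volume of users referred through Google searches will be larger than that of users referred through Reddit". Hypothesis 4 is that "users referred through Reddit will spend more time on the website and click on a higher number of links than users referred through Google searches". The acceptability hypotheses contrast types of user, not sources. Study Objectives and Specific Aims words the aim for user characteristics neutrally, as a search for possible differences.

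**The concern.** The article names a test, and that test does not fit much of what it is meant to compare. There are three mismatches:

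- **Direction.** A 1-tailed test needs a direction fixed in advance. Return rate, acceptability and user characteristics have none by source, and the aim for characteristics is neutral.
- **Scale.** A t test compares means. Location and language have no meaningful mean.
- **Replication.** A t test needs variation within each group. User volume, taken as one total per source, has none.

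Recruitment, Sample, and Participants says the comparison will help to judge which platform suits dissemination of later interventions. For the affected variables, either the result would depend on an arbitrary choice (the tail, or the category codes) or there would be no result.

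**Working it through.** The article states no alpha, sample size or power for this comparison, so there is no figure of its own to reproduce. Alpha below is an assumption, and all counts are invented for illustration.

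**1. Which comparisons have a predicted direction by source** (Outcomes and Measures, Table 2)

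| Variable | Predicted direction | Type |
|---|---|---|
| User volume | Google higher | one count per source |
| Time, clicks | Reddit higher | numeric |
| Return rate | none | binary |
| Acceptability score | none | numeric |
| Age | none | numeric |
| Gender, self or other | none | categorical, few levels |
| Location, language | none | nominal, many levels |

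**2. What a fixed tail does when the difference runs the other way.** Take a true difference of 2.8 standard errors (SE) and the normal approximation, with Φ the standard normal distribution function.

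- Two-sided test, alpha 0.05 (critical value 1.96): power ≈ Φ(2.8 − 1.96) = Φ(0.84) = 0.80.
- One-sided test, alpha 0.05 (critical value 1.645), right direction: Φ(2.8 − 1.645) = Φ(1.155) = 0.876.
- The same test, wrong direction: Φ(−2.8 − 1.645) = Φ(−4.445) = 4.4 × 10⁻⁶.
- One-sided alpha 0.025 (critical value 1.96), wrong direction: Φ(−4.76) = 9.7 × 10⁻⁷.

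**3. What happens if the tail is chosen after seeing the data.** The type I error is 2 × alpha: 2 × 0.05 = 0.10, or 2 × 0.025 = 0.05. Nothing in the article says that this will be done. Leaving the direction unstated leaves room for it.

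**4. Nominal variables.** Take four categories, with Reddit counts 100, 50, 100, 50 and Google counts 50, 100, 50, 100. Every expected count is 75, so chi-square = 8 × 25²/75 = 66.7 on 3 degrees of freedom, p = 2 × 10⁻¹⁴, however the categories are numbered. The t test depends on the numbering:

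- Codes 1, 2, 3, 4: means 700/300 = 2.33 and 800/300 = 2.67, p = 2 × 10⁻⁴.
- Codes 1, 4, 2, 3: means 650/300 = 2.17 and 850/300 = 2.83, p = 9 × 10⁻¹⁴.
- Codes 1, 3, 4, 2: means 750/300 = 2.50 in both groups, p = 1.0.

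**5. Binary variables, for contrast.** With 120/300 against 100/300, the t test gives p = 0.0905 and chi-square gives p = 0.0902. The t test does little harm here in large samples.

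**6. User volume.** With one total per source, degrees of freedom = 1 + 1 − 2 = 0, and the software returns no statistic. Splitting the year into four quarters gives 4 + 4 − 2 = 6 degrees of freedom, but the analysis section does not say that this will be done. A count comparison works on the totals directly. For 550 against 450, the ratio is 550/450 = 1.22 and the one-sided exact binomial p is 0.0009.

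**The case against.** The strongest reply is that the outcome sentence only gives an example, so other bivariate tests stay open, and that a journal article commonly leaves the test for each variable to a fuller plan. This stands in part. It rules out saying that every outcome will be tested 1-tailed. It does not cover the second sentence, which assigns sociodemographic differences to t tests outright, and the one example given suits only some of the outcomes.

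A reader might infer that 1-tailed tests are ruled out because hypotheses 3 and 4 point in opposite directions. They are not. Each hypothesis concerns different outcomes and can have its own 1-tailed test in its own predicted direction. The fault is that no direction is attached to any test.

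A reader might also infer that the characteristics will be tested 1-tailed, or that most demographics cannot be tested at all. The sentence on characteristics does not repeat the tail. Age is numeric, and two-level variables behave almost as under chi-square. The scale problem is confined to multi-category variables, chiefly location and language.

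On volume, no sentence specifically promises a t test of total users. Referral source is also listed under descriptive statistics, and the data will be examined every three months. Plain reporting or quarterly totals would avoid the problem, so the impossibility holds only for a single total per source.

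Finally, the article promises confidence intervals for each outcome, so an unexpected difference need not go unseen. That is fair, although it does not say whether the intervals are two-sided.

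**Conclusion.** The point holds, at moderate severity. The named test is a poor default for return rate and acceptability, which have no predicted direction by source. It is not meaningful for location and language, and it cannot be computed for volume as one total per source. It is legitimate for time and clicks under hypothesis 4 if the direction is stated. Age and acceptability scores can keep a mean comparison, made two-sided.

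The error figures are conditional. The 4 in a million needs a tail fixed the wrong way, a one-sided alpha of 0.05 and a true difference of 2.8 SE. The doubled false-positive rate needs the tail to be chosen after looking. The article supports neither as a planned practice, so these figures show what an unstated direction permits and do not forecast what will happen.

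Two stronger readings lack support. One is that the plan must be changed before the study can proceed. It is a descriptive feasibility study without randomization or a target sample size, and no decision rule depends on these p values. The other starts from the statement "We will be able to identify whether participants came from Reddit or Google and treat them as 2 different samples" and infers that the samples overlap because a user may arrive by both routes. How repeat visitors are attributed to a source is a detail that an article may leave to a fuller plan, and the document gives no figure for overlap.

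**What to change.** Replace the two sentences with a short rule by type of variable:

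- Use two-sided tests with 95% CIs by default. Keep a one-sided test, if wanted, only for reach hypotheses 3 and 4, with its direction written down (Google higher for volume; Reddit higher for time and clicks).
- For gender, location, language, self or other, and return rate, use chi-square or exact tests with differences in proportions.
- Report volume as a ratio of user counts with a binomial or Poisson CI, or descriptively.
- For age, time, clicks and acceptability scores, compare means. Use robust or bootstrap CIs for time and clicks, which are likely to be skewed. This also handles users with zero clicks without a log transformation.

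The cost is about two sentences and slightly more analysis work, with no new data and no design change. Where a two-sided test replaces a one-sided one at the same alpha of 0.05, the confidence limit lies 1.96 rather than 1.645 SE from the estimate (1.96/1.645 = 1.19, so 19% farther). Power at 2.8 SE in the predicted direction falls from 87.6% to 80%.

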### The MOUD Hub

We sought to create a web-based resource that provides user-friendly, reliable information to address barriers to MOUD at different steps of the care continuum, tailored to support both people living with OUD and friends and family in navigating the different stages of treatment and their respective challenges. We chose motivational interviewing (MI) as a guiding intervention. MI follows harm reduction principles to help promote progression along stages of the transtheoretical model of behavior change: precontemplation, contemplation, preparation, action, maintenance, recurrence (or relapse), and termination stages [23]. MI provides a nonjudgmental space that meets people where they are in managing their OUD and finding motivation toward behavior change.

We followed the Conceptual Framework of Access to Health by Levesque et al [24] to classify the different barriers across the MOUD care continuum, which maps onto the transtheoretical model of behavior change and consists of assessing one’s health care needs, desire for care, seeking health care, reaching care, using care, and health care consequences. The Access to Health framework comprises 5 domains characterizing health care service: approachability, acceptability, availability and accommodation, affordability, and appropriateness. These domains are connected to the 5 abilities of persons to receive health care, which include the ability to perceive, seek, reach, pay, and engage.

Therefore, we developed the *MOUD Hub*, a web-based resource to help reduce barriers to accessing and remaining on MOUD care [25]. Our goal was to create a resource that would cater to all people with OUD, including those not yet considering treatment or having stopped treatment, to facilitate linkage to services and resources across multiple needs, such as prevention services, harm reduction tools, treatment resources, and social resources. This paper describes the protocol of how this website was conceptualized and created, along with how we plan to disseminate it and assess its feasibility by characterizing its reach, use patterns, and acceptability [26].

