**Figure 1 figure1:**
[figure not shown]
A snapshot from the MOUD Hub’s stages of change wheel. When users click on a specific stage, a pop-up appears with a brief quote and information related to that stage. Users can click “see more” and will be taken to the stage’s specific page. MOUD: medications for opioid use disorder.

As in an MI session with a counselor, the *MOUD Hub* does not indicate to the user which stage of change they might be at and instead relies on their self-identification based on the stages’ descriptions and associated quotes provided on the home page. The reasoning behind this is 2-fold. First, we wanted to stay aligned with the principles of MI, including the horizontal relationship between the client and the counselor and the respect for the client’s capacity to identify the right tools for themselves (rather than a top-down educational approach in which the counselor informs the client of their condition and the steps they need to follow to resolve it). Second, some users might be friends or family of people living with OUD, and it might be harder for them to accurately complete an assessment, leading to inaccurate guidance. In both cases, this open approach might lead users to explore several stages before focusing on one stage, which could increase their understanding of the process of change.

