**Recurrence (or relapse) stage^j^**			
	Stigma or shame around recurrence. The belief that recurrence is a “failure” [35]	Research on recurrence as a natural occurrence of OUD and opportunity for readjustment	Approachability Ability to perceive Ability to engage
	Belief that recurrence is long-term	How to return to treatment	Approachability Acceptability Appropriateness
	Lack of strategies to prevent recurrence [32]	Create a recurrence prevention plan	Ability to seek Ability to engage
	High risk of overdose during recurrence	Revisit harm reduction resources	Approachability Ability to perceive

^a^Precontemplation stage MI check-in questions: readiness rulers [36]—How important is it for you to change your opioid use? What made you choose that number and not a lower one? What would help you pick a higher number? How confident are you in making this change? What would help you be more confident?

^b^OUD: opioid use disorder.

^c^MOUD: medications for opioid use disorder.

^d^HCV: hepatitis C virus.

^e^Contemplation stage MI check-in questions: How does your current opioid use affect your life, relationships, career, and future goals? How would treatment help you resolve some of those and help you achieve your goals?

^f^Preparation stage MI check-in questions: What are the ways to address some of the challenges you are worried you may face? What are the steps you may need to take to receive treatment?

^g^Action stage MI check-in questions: What has been working well for you? Are there any places that you need to strengthen to help your progress?

^h^Maintenance stage MI check-in questions: What challenges have you been encountering? What are practical ways to address them? Can you name 3 things that have improved since starting treatment?

^i^Termination stage MI check-in questions: readiness rulers [36]—How confident are you in making this change?

^j^Recurrence (or relapse) stage MI check-in questions: How has this relapse gotten me closer or farther away from my treatment goals? What do you think you need to help you in your next steps?

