**Quantitative measures**		
	Volume of users (GA^a^)	Proportion of users who return to the website (GA)
	Average time spent on the website (GA)	Acceptability of Intervention Measure questions (PS^b^; Figure 4)
	The average number of resources the users clicked on in different stages (GA)	—^c^
	Total number of times a resource was clicked within each stage (GA)	—
	User demographics (age, gender, location, language, and accessing the website for themselves or for a friend or family member; GA and PS)	—

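### No stated test answers reach hypothesis 1: the stage test is one stage against all others on accesses, the hypothesis is a grouped contrast on link clicks

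*Protocol article*

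**What the plan says.** In the protocol article, Outcomes and Measures, the first reach hypothesis is that "users will most frequently click on links related to the precontemplation or contemplation phases of MOUD use". The comparison side is given in the same sentence with the words "as opposed to links related to the preparation, action, and maintenance phases". Five of the website's stages are named. The introduction (The MOUD Hub) lists seven: "precontemplation, contemplation, preparation, action, maintenance, recurrence (or relapse), and termination stages".

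The Statistical and Qualitative Analyses section plans unnamed statistical tests of two kinds. The stage test looks for "significant differences in the number of times each stage was accessed (vs all other stages". The resource test looks for differences "in the number of times each specific resource was clicked on (vs other resources within that stage". The only named tests are t tests, and they concern Reddit against Google and differences in sociodemographic characteristics and use patterns.

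Table 2 lists "Total number of times a resource was clicked within each stage (GA" as a measure. It also lists a per-user average of resources clicked by stage, but the analysis section ties no between-stage test to it. On how users move through the site, the section on motivational interviewing and the transtheoretical model says that "this open approach might lead users to explore several stages before focusing on one stage".

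**The concern.** The study writes down a directional hypothesis about which part of the care pathway attracts clicks, and then plans comparisons of a different shape on a different quantity. A significant result for one stage against the rest would neither confirm nor refute it. Whoever reports the study would have to choose, after seeing the data, how to turn seven stage results into one answer.

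A second issue sits alongside. The tests are worded as counts of accesses or clicks, and one user can supply many. If the analyst took each access as a separate observation, the error rate could be wrong.

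The study is descriptive and has no target sample size, so no power claim is at stake. What is at stake is how the first reach hypothesis is read, and the evidence available when the website is revised every 3 months.

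**Working it through.** **Hypothesis and tests side by side**

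| | Hypothesis 1 | Stage test | Resource test |
|---|---|---|---|
| Quantity | link clicks | stage accesses | resource clicks |
| One side | precontemplation and contemplation | one stage | one resource |
| Other side | preparation, action, maintenance | the six other stages | other resources in the same stage |

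The stage test differs in the quantity, in having the second early stage in the comparator, and in including termination and recurrence. The resource test never compares stages.

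**Can the answers diverge?** Suppose, for simplicity, that clicks are proportional to accesses. Let each early stage receive e, each of the three later stages l, and termination and recurrence t each. The document does not say whether the rest is summed or averaged; take the average of the six others.

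- An early stage stands out if e > (e + 3l + 2t)/6, that is 5e > 3l + 2t.
- Hypothesis 1, read on totals, holds if 2e > 3l, that is e > 1.5l.
- If t = l, the stage test needs only e > l. For e between l and 1.5l, both early stages stand out and the hypothesis is false on totals.
- If t = 0, the stage test needs only e > 0.6l.
- At the boundary e = 1.5l, the stage test needs 7.5l > 3l + 2t, that is t < 2.25l. With t above that, the hypothesis can hold while neither early stage stands out.
- If all seven stages are equal, the stage test has nothing to find, yet the early share of the five named stages is 2/5 = 40% against 60%.

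So the divergence can go either way, and it depends partly on two stages that the hypothesis leaves out.

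**Several accesses per user.** The document gives no error rate to reproduce. Assume m accesses per user, within-user correlation ICC, and a two-sided 5% test on single accesses. The design effect is DEFF = 1 + (m − 1) × ICC, and the actual error is 2 × [1 − Φ(1.96/√DEFF)].

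| m | ICC | DEFF | Actual error |
|---|---|---|---|
| 3 | 0.05 | 1.1 | 6.2% |
| 5 | 0.2 | 1.8 | 14.4% |
| 10 | 0.5 | 5.5 | 40.3% |
| 5 | −0.1 | 0.6 | 1.1% |

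The last row is there because the sign is open: a user who samples several stages spreads accesses out (negative correlation), whereas one who settles on a stage concentrates them (positive). In a simulation with positive correlation (500 users, 4,000 runs), the access-level test rejected in 6.7% (m = 3, ICC 0.05), 14.1% (5, 0.2), 23.1% (10, 0.2) and 25.6% (5, 0.5) of runs. A test on per-user proportions rejected in 5.1% to 5.4%. All values of m and ICC are assumptions.

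**Stage content.** Table 1 has 4, 2, 4, 3, 3, 1 and 4 rows for precontemplation, contemplation, preparation, action, maintenance, termination and recurrence. If each row drew clicks equally, the early share of the five named stages would be 6/16 = 37.5%. With the 11 preparation tabs in the Figure 2 caption it would be 6/(6 + 11 + 3 + 3) = 26.1%. Counting the separate items listed in the rows gives roughly 15 early and 18 later, 15/33 = 45%. Against 40% by number of stages, even the direction of a content effect is unsettled.

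**The case against.** The fairest defence is that this is a descriptive feasibility study in a condensed article. The test and its unit are unnamed, and a fuller plan could set them. Much of that stands, and it rules out several stronger readings that a reader might infer:

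- *Clicks are treated as independent.* The document never says so. It words the tests as counts and leaves the unit open.
- *Intervals will be too narrow.* The sign of the within-user correlation is unknown, and users who explore several stages could make a naive test conservative.
- *Unequal numbers of links bias the planned tests.* The resource test stays within a stage, so link numbers across stages do not enter it. The stage test counts accesses, and link numbers matter there only if theme pages count as accesses. Table 1 rows are barriers, not links.
- *Clicks cannot be assigned to a stage.* It is true that "Create a recurrence prevention plan" appears under more than one stage, but Table 2 already plans click totals within each stage.
- *Multiplicity is ignored.* The article is silent on it, which is not a stated choice to leave the tests unadjusted.
- *Significance will decide website changes.* The Results section says that findings on the listed outcomes will inform modification; it does not make significance the criterion.

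The mismatch survives all of this. Both the hypothesis and the contrasts are written out in the article, and they differ. That is not a detail left for later.

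**Conclusion.** The point holds as a mismatch between a stated hypothesis and the stated tests, and it needs no numerical assumption. Under the simplifications shown, an early stage can stand out at anything from 0.6 to 1.5 times the traffic of a later stage while hypothesis 1 fails on totals, and the reverse can also happen.

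The clustering part is conditional. If single accesses were the unit, a nominal 5% test could run from about 1% to about 40% over the assumed range, and nothing in the document says where in that range, or on which side of 5%, the study would fall. This supports naming the unit; it does not support saying that the planned analysis is invalid.

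**What to change.** In Statistical and Qualitative Analyses, add one prespecified contrast for reach hypothesis 1:

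- For each user, take link clicks in precontemplation plus contemplation, minus link clicks in preparation plus action plus maintenance, using the stage attribution already planned in Table 2.
- Report the mean difference with a user-level confidence interval, for example from a bootstrap that resamples users. This mean is the difference in total clicks divided by the number of users, so it keeps the hypothesis on totals and changes only how its uncertainty is measured.
- State that termination and recurrence lie outside the contrast, and that zero means equal totals over two and three stages.
- Show clicks per available link as a sensitivity analysis, since the stages differ in content. It asks a different question and should not replace the main contrast.
- Report the remaining stage and resource comparisons descriptively, with user-level intervals.

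The cost is mostly wording. User-level Google Analytics data must be extractable, which should be confirmed before launch, and intervals may be wider. No extra recruitment is needed.
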